**FIGURE 2 F2:**
[figure not shown]
The schematic diagram of the patient timeline.

### Efficacy Outcomes

In this trial, the primary outcome is neurological deficit amelioration defined as a change in the NIHSS score from baseline to 10 post-randomization days. Secondary outcomes will be as follows: 1) the proportion of patients with early neurological improvement (NIHSS score 0–1) at 10 post-randomization days; 2) patients’ subjective feelings measured at 10 post-randomization days using the Patient-Reported Outcomes scale for Stroke (PRO-Stroke), which is a well-validated scale suitable in Chinese patients for assessing stroke and treatment effects on physical function, psychological change, social engagement, and treatment satisfaction (Wang et al., 2012a; Wang et al., 2012b; Wang et al., 2012c); 3) proportion of patients with life independence (90-days modified Rankin Scale [mRS] score ≤1); 4) proportion of patients with a favorable outcome (90 days BI score ≥90); and 5) patients’ quality of life measured using the Stroke-Specific Quality of Life (SS-QOL) at 90 days.

### Biological Outcomes

We will perform between-group comparisons of the changes in ICAM-1, IL-6, TNF-α, and MMP-9 levels from baseline to 10 post-randomization days.

### Safety Outcomes

The safety outcome will include any adverse events (AEs), SAEs, and clinically meaningful changes in vital signs or laboratory parameters during the trial period.

### Follow-Up Procedures

The EXPECT trial contains four visits including time at randomization (baseline), 10 ± 2 days after randomization, 30 ± 3 days, and 90 ± 7 days after stroke onset. At baseline, we will evaluate demographic characteristics, routine laboratory tests, non-contrast CT/MRI, vessel imaging (carotid artery ultrasound/transcranial Doppler imaging/MR angiography), electrocardiogram (ECG), and NIHSS. At 10 ± 2 days, we will perform assessments using the PRO-Stroke, repeated routine laboratory tests, ECG, and NIHSS. Biological samples will be collected at both baseline and 10 ± 2 days. The mRS, BI, and SS-QOL scores will be determined at 30 ± 3 days and 90 ± 7 days. Finally, vital signs and complications will be recorded at these four visits; on the other hand, AEs and SAEs will be recorded at any time during the trial.

### Data Collection and Management

Data collection and management will be performed in collaboration with clinical doctors and clinical research coordinators. All investigators in charge of patient recruitment, outcome assessment, data collection, and serum sample collection will receive pre-recruitment standardized training regarding this trial’s standard operating procedures. Investigators in all medical centers will make a reasonable effort to follow-up with the patient throughout the study period. Information obtained from patients will be recorded in the investigative case form by investigators; subsequently, the clinical research coordinator will perform data entry into electronic case report forms using a unique login ID. All patient-related information will be stored in locked file cabinets with limited access at medical centers. All serum samples, reports, data collection, and administrative forms will be only identified using a coded ID number to maintain participant confidentiality.

### Quality Control and Data Monitoring

The Steering Committee will be responsible for the scientific content of the protocol, overseeing the study operations, supervising the intra-study data sharing process, and preparing the primary manuscript and other publications arising from the EXPECT trial. Two contract research organizations will regularly perform data monitoring and data quality control. Data analysis will be completed by a third-party statistical unit (Tianjin University of Traditional Chinese Medicine).

### Adverse Events Management

All AEs will be evaluated for their association with investigational medicine; subsequently, they will be treated, recorded, and followed-up until recovery or stabilization. The investigators will report any SAE to the ethics committee, contract research organization, principal investigator, and China Food and Drug Administration.

### Sample Size Calculations

Based on a previous study that reported a mean decrease in the NIHSS score of 3 and 2.1 in the PNS and control groups, respectively, and a standard deviation of 2.5 (Wang, 2009), this trial will require 480 patients with a power of 90%, two-sided α of 0.05, and a 20% dropout rate to test the hypothesis that PNS is superior to placebo in decreasing the NIHSS score at 10 post-randomization days in patients with AIS.

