### Randomization, Allocation, and Blinding

The investigators will randomize 480 eligible patients and assign them to the intervention and control groups at a 1:1 ratio using block randomization with stratification according to medical centers. The randomization schedule will be generated by an independent statistician using SAS software version 9.4 (SAS Institute Inc.) and kept in sealed, sequentially numbered, opaque envelopes. Investigational medicine blinding will be completed at a pharmaceutical factory based on the randomization schedule and sent to medical centers along with the emergency envelopes. The block size will be closed to ensure concealment throughout the entire trial period. All investigators, participants, caregivers, and data analysts will be blinded to the treatment assignments throughout the trial until the blind codes are unconcealed. Investigators can request emergency unblinding in case of serious adverse events (SAEs) suspected to be associated with investigational medicine. Figure 1 presents a flowchart of the EXPECT trial.

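### The printed sample-size inputs require about 408 to 410 randomized patients, not 480; on those inputs 480 gives about 94% power, and the route to 480 is not stated

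*Protocol article*

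**What the plan says.** The Sample Size Calculations section of the protocol article takes its assumptions from a cited earlier study: "a mean decrease in the NIHSS score of 3 and 2.1 in the PNS and control groups, respectively, and a standard deviation of 2.5". From these it concludes that "this trial will require 480 patients with a power of 90%, two-sided α of 0.05, and a 20% dropout rate". The Randomization, Allocation, and Blinding section says that the investigators will "assign them to the intervention and control groups at a 1:1 ratio".

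The sample-size section mentions no superiority margin, no allowance for a non-parametric test, no adjustment for centre and no deliberate rounding up. The Statistical Analysis Plan section compares the change in NIHSS by t-test or Mann-Whitney test, sets two-sided significance at 0.05, and imputes missing primary outcome data by last observation carried forward (LOCF).

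**The concern.** The section prints every input that a two-sample comparison of means needs, so the total can be checked directly. It does not follow from those inputs. This is not a matter of something left to a fuller document: the printed sentence says that a particular number is required under particular assumptions, and under those assumptions it is not.

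The credibility of the main planning figure is at stake. The sentence is likely to be carried into the results paper, and a reader who recalculates it will find either that an input was left out or that the power is misstated. The rationale for the number of patients asked to take part should be reproducible.

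**Working it through.** **Inputs**
- Difference: 3 − 2.1 = 0.9 points (Sample Size Calculations).
- Standard deviation: 2.5, read as common to both arms (same section).
- Two-sided alpha 0.05, power 90%, dropout 20% (same section).
- Allocation 1:1 (Randomization, Allocation, and Blinding).

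**Attempt to reproduce 480**

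n per arm = 2 × (z for 1 − α/2 + z for power)² × (SD / difference)²

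= 2 × (1.960 + 1.2816)² × (2.5 / 0.9)² = 162.2, rounded up to 163.

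The exact t calculation gives 164. Allowing for dropout:
- 163 / 0.8 = 203.75, so 204 per arm and 408 in total.
- 164 / 0.8 = 205 per arm and 410 in total.

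The stated 480 is 70 to 72 patients, or about 17%, above this.

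**The same check in the other direction**

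480 × 0.8 = 384 evaluable, or 192 per arm. The standard error is 2.5 × √(2/192) = 0.255, and 0.9 / 0.255 = 3.53. Power = Φ(3.53 − 1.96) = 94.1% (exact t: 94.0%). With all 480 evaluable, power is 97.6%.

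**Other conventions, with difference 0.9 and SD 2.5**

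| Variant | Total randomized |
|---|---|
| Dropout applied as × 1.2 instead of / 0.8 | 392 to 394 |
| One-sided alpha 0.05, 90% power | 333 |
| 80% power, two-sided | 305 |
| 85% power, two-sided | 348 |
| 95% power, two-sided, / 0.8 | 503 |
| 95% power, two-sided, × 1.2 | 483 |
| Mann-Whitney, efficiency for normal data (3/π, about 0.955) | 426 to 430 |
| Mann-Whitney, worst-case efficiency (0.864) | 470 to 476 |
| Two-sided alpha 0.025, 90% power | 480 |

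The last row is 2 × (2.2414 + 1.2816)² × (2.5 / 0.9)² = 191.5, so 192; 192 / 0.8 = 240 per arm. The ranges in the Mann-Whitney rows reflect rounding and whether the normal or the t calculation is the starting point.

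**What would make 480 correct at 90% power, changing one input at a time**
- Difference: 2.5 × 3.2415 / √96 = 0.83 points.
- SD: 0.9 × √96 / 3.2415 = 2.72.
- Dropout: 1 − 326/480 = 32%.

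**Power if dropouts are kept at zero change**

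The Follow-Up Procedures section lists the NIHSS only at baseline and at the day-10 visit, so LOCF for a missing day-10 score would carry the baseline score forward, a change of zero. Suppose this applies to 20% of each arm and all 480 are analysed:
- Difference: 0.8 × 0.9 = 0.72.
- Variance, PNS arm: 0.8 × 6.25 + 0.16 × 3² = 6.44.
- Variance, control arm: 0.8 × 6.25 + 0.16 × 2.1² = 5.71.
- Average 6.07, so SD about 2.46.
- Power with 240 per arm: 0.72 / (2.46 × √(2/240)) = 3.20; Φ(3.20 − 1.96) = about 89%.
- For 90% power: 2 × 3.2415² × 6.07 / 0.72² = 246.2, so 247 per arm or 494 in total.

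**The case against.** There are four serious arguments on the other side.

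**Rounded inputs.** The means and SD come from a source that is not shown and are printed to one decimal at most. If both means are rounded to one decimal, the true difference could lie between about 0.80 and 1.00. A difference of 0.83 with SD 2.5 gives 191 per arm and 478 in total. So unrounded values could yield about 480 with alpha, power and N all as stated. This stands as a possible explanation, and it means one cannot conclude that alpha, power or N must be wrong. It does not make the sentence correct as printed, because a reader has only the printed values.

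**A non-parametric allowance.** The Mann-Whitney test is permitted, and its worst-case efficiency brings the total to 470 to 476. This also stands as a possibility. However, the section describes a calculation from means and an SD and mentions no such allowance.

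**LOCF.** A reader might infer that the trial enrols about 70 patients more than it needs. That holds only if dropouts leave the analysis. If they stay in at zero change, 480 gives about 89% power, close to the stated 90%, and there is no surplus. This argument stands in full against the claim of an excess. It does not rescue the sentence, which does not describe the calculation in that way.

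**Harmlessness.** On the printed inputs the trial is larger than required, and planned power does not alter the estimate, interval or p-value. This is right, and it limits the severity.

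**Conclusion.** The stated total does not follow from the stated inputs: 408 to 410 are required, against 480 stated. With 384 evaluable patients, 480 corresponds to about 94% power. This rests on a common SD of 2.5, a two-sample comparison of means, and dropouts being excluded from the analysis.

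Because the two-sided alpha of 0.025 reproduces 480 exactly, a reader might infer that alpha was halved twice. The document does not support that as a finding. Both the Sample Size Calculations and the Statistical Analysis Plan sections give two-sided 0.05, and other unstated routes come close to 480. The cause is unknown.

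Nor should 94% be taken as the power of the planned analysis without qualification. The full analysis set requires available efficacy data, while LOCF imputes missing primary data, so it is unclear how many dropouts would be imputed. The two cases, all dropouts excluded or all kept at zero change, give about 94% and about 89%.

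This is a reporting error of moderate severity. On the printed inputs it is in the conservative direction, and it gives no reason to change enrolment.

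**What to change.** Keep N = 480 and correct the sentence in one of two ways.

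1. State the input or adjustment that was actually used to reach 480, such as unrounded means and SD, a non-parametric allowance, a different alpha or deliberate rounding up.
2. If none can be documented, restate the power: 480 randomized with 384 evaluable gives about 94% power at two-sided alpha 0.05 for 0.9 points with SD 2.5. Equivalently, this is 90% power for about 0.83 points, or for 0.9 points with an SD up to about 2.7. Add that if dropouts are kept in the analysis by LOCF at zero change, power is about 89%.

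The first is preferable if the original calculation can be retrieved. The cost is one corrected sentence, repeated wherever the sample-size statement is reused. No patients are added or removed, and no test or significance level changes.

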### Statistical Analysis Plan

All randomized patients who receive at least one treatment dose and have safety outcome data will be included in the safety set. All patients in the safety set will be included in the full analysis set if efficacy outcome data are available. All patients in the full analysis set who are deemed to have no major protocol violations will be included in the per-protocol set. Efficacy and safety analyses will be performed according to the intention-to-treat principle. Additionally, per-protocol data analysis will be conducted as a reference. The last observation carried forward approach will be used to impute missing data of primary outcome. Regarding the primary outcome variable, between-group comparisons of the change in NIHSS score will be performed using Student’s *t*-test or Mann-Whitney *U* test, as appropriate. Regarding secondary outcome variables, between-group comparisons of the proportion of patients with an NIHSS score of 0–1, mRS grade ≤1, and BI score ≥90 will be performed using the chi-square test or Fisher exact test. Further between-group comparisons of the PRO-Stroke and SS-QOL score, as well as changes in biological indexes, will be compared using the *t*-test or Mann-Whitney *U* test. Moreover, between-group comparisons of the incidence of AEs will be compared using the chi-square or Fisher exact test. The effect of missing data on the results will be assessed through sensitivity analysis. All statistics will be 2-sided and statistical significance will be set at *p* < 0.05. Statistical analyses will be performed using SAS software version 9.4 (SAS Institute Inc.).

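### The full analysis set depends on efficacy data being available, which does not fit the stated intention-to-treat principle and drops early losses from the primary comparison

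*Protocol article*

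**What the plan says.** All the rules on analysis sets stand in the Statistical Analysis Plan section of the protocol article. The safety set comes first: "All randomized patients who receive at least one treatment dose and have safety outcome data will be included in the safety set". The full analysis set is drawn from it: "All patients in the safety set will be included in the full analysis set if efficacy outcome data are available". The per-protocol set is the full analysis set without major protocol violators. No set of all randomised patients is defined.

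The section then states the principle, "Efficacy and safety analyses will be performed according to the intention-to-treat principle", and the rule for missing values, "The last observation carried forward approach will be used to impute missing data of primary outcome". It adds: "The effect of missing data on the results will be assessed through sensitivity analysis". Neither the method nor the population of that sensitivity analysis is given.

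Under Efficacy Outcomes the primary outcome is "a change in the NIHSS score from baseline to 10 post-randomization days". Follow-Up Procedures schedules the NIHSS at baseline and once more: "At 10 ± 2 days, we will perform assessments using the PRO-Stroke, repeated routine laboratory tests, ECG, and NIHSS". The later visits carry other scales: "The mRS, BI, and SS-QOL scores will be determined at 30 ± 3 days and 90 ± 7 days".

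**The concern.** Intention-to-treat means that patients are compared as randomised, whatever happens to them afterwards. Here, entry to the efficacy set depends on events after randomisation, and one of those events is whether an outcome was obtained. A patient who deteriorates, dies or withdraws before any assessment fails the condition and leaves the comparison. If such losses are more frequent in one arm, or involve worse patients in one arm, the remaining groups are no longer the randomised ones, and the arm that lost more poor outcomes looks better than it should.

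The clause also bears on the imputation rule. A set that requires outcome data, combined with a rule for imputing outcome data, makes sense only once it is clear which data must be present. The article does not say, so the analyst must choose who is in the primary analysis.

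**Working it through.** **The plan's own figures.** Sample Size Calculations gives mean NIHSS decreases of 3 and 2.1 (difference 0.9), SD 2.5, 90% power, two-sided α of 0.05, 20% dropout and 480 patients. The usual formula gives n = 2 × (1.960 + 1.282)² × (2.5/0.9)² ≈ 162.2, so 163 per arm and 326 in total, and 326/0.80 = 407.5, so 408. The stated 480 is not reproduced. That is a separate matter and nothing below depends on it; 480 and 20% are used as stated.

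**Upper bound on patients affected.** 0.20 × 480 = 96, leaving 480 − 96 = 384.

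**The two natural readings of the availability condition.**

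| Reading | Who leaves the set | Whom carrying forward acts on |
|---|---|---|
| Day-10 NIHSS must be present | Everyone missing it, up to 96 | Nobody |
| Any post-baseline efficacy measure must be present | Only patients with none | Those missing the day-10 NIHSS who have PRO-Stroke or day-30 or day-90 scores |

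The documents do not give the split between the last two groups; each could lie anywhere from 0 to 96. A patient who dies or withdraws early with nothing recorded is out on both rows.

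**What carrying forward does.** Only one NIHSS is scheduled after baseline. When it is missing, the last earlier value is normally the baseline score, so the imputed change is baseline − baseline = 0.

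**Size of the possible bias.** Let q be the share lost in an arm, C the mean improvement of those retained and D that of those lost. The all-randomised mean is M = (1 − q)C + qD, so C = M + q(C − D). If C − D is the same in both arms, the retained-patient difference is off by (q₁ − q₂) × (C − D). Take C − D = 3 points (assumed; not in the documents):

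- imbalance of 5 percentage points: 0.05 × 3 = 0.15, and 0.15/0.9 = one sixth of the target;
- imbalance of 10 percentage points: 0.10 × 3 = 0.30, and 0.30/0.9 = one third;
- no imbalance: 0.

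A second illustration fixes the outcome of those lost. Assume no true effect, with an all-randomised mean improvement of 2.1 in both arms. The retained mean is then (2.1 − qD)/(1 − q).

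- D = 0, losses 25% against 15%: 2.1/0.75 − 2.1/0.85 = 2.80 − 2.47 = 0.33.
- D = 0, losses 10% against 5%: 2.1/0.90 − 2.1/0.95 = 2.33 − 2.21 = 0.12.
- D = −4 (worsening by 4 points), same two pairs: 0.96 and 0.36.
- 20% lost in each arm: 0 for either D.

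**Power.** With 384 observed cases the standard error is 2.5 × √(2/192) = 0.255, and Φ(0.9/0.255 − 1.96) ≈ 0.94. If all 480 are analysed with 96 set to a change of 0, the difference shrinks to 0.80 × 0.9 = 0.72. The arm variances are 0.8 × 2.5² + 0.8 × 0.2 × mean², that is 6.44 and 5.71, so the standard error is √((6.44 + 5.71)/240) = 0.225 and the power about 0.89.

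**The case against.** The strongest reply is that the two rules can work in sequence: the first decides who is in the set, and the second fills a missing day-10 NIHSS for those in it. On the broader reading this gives the imputation rule work to do, which makes that reading the more natural one. A reader might infer that the set holds completers only, that the section lays down two incompatible primary analyses, or that hardly anyone is left to impute. The text does not support these as general statements. They follow only if the condition means the day-10 NIHSS, which the article does not say. On the broader reading, patients who stop study drug but are assessed stay in, as do those who miss day 10 but attend later, and protocol violators are removed only from the per-protocol set.

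Other parts of the reply also stand. Leaving out never-dosed patients is defensible in a double-blind trial. Requiring safety data should exclude very few, because adverse events are recorded throughout and vital signs at all four visits. The trial recruits inpatients, and the Discussion argues that the short interval to the NIHSS assessment limits loss, so 96 may be well above the true number. Unequal losses are possible under blinding but are not to be presumed.

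What does not stand is that this is merely detail left to a fuller document. The article states the rule and states a principle that the rule does not meet. Counting the baseline NIHSS as available efficacy data would make the condition empty, and the sentence does not read that way. Deaths could enter on the broader reading if a score assigned to death were counted as available data, but the article provides no such rule. The promised sensitivity analysis has no stated population or method, so it does not settle who is in the primary analysis.

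**Conclusion.** The point holds in a limited form. As written, the primary efficacy set depends on outcome availability and is nevertheless described as intention-to-treat. On either natural reading, patients who die or withdraw early without an assessment are dropped. How many others are dropped, and how many are imputed, turns on an undefined condition.

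The number affected is at most 96 of 480. Under the assumed 3-point deficit, bias is 0.15 to 0.30 points for imbalances of 5 to 10 percentage points, and zero when losses and deficit are equal in the two arms. The deficit and the imbalances are assumptions. The harm is possible selection bias and analyst discretion, not loss of power. It should be settled before unblinding.

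**What to change.** Define the primary efficacy set as all randomised patients, excluding at most those never dosed, analysed in the arm assigned. Delete the condition on efficacy data, and do not make the efficacy set depend on safety data.

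Deleting the clause alone is not enough. Sent to the existing imputation rule, the restored patients would normally receive a change of 0, deaths included. State in the primary analysis how a missing day-10 NIHSS is handled, including after death. Replace last observation carried forward, for example by multiple imputation with a rule for deaths fixed in advance. Report the observed-data and baseline-carried-forward analyses as sensitivity analyses, which would also give content to the one already promised.

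The cost is a few sentences in the protocol and the analysis plan and a little more analysis work. No new data are needed.

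### With one NIHSS after baseline, LOCF scores any imputed patient as exactly no change, and the full analysis set rule leaves open who is imputed and who is excluded

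*Protocol article*

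**What the plan says.** Under Efficacy Outcomes, the primary outcome is "a change in the NIHSS score from baseline to 10 post-randomization days". Under Statistical Analysis Plan, the rule for missing values is "The last observation carried forward approach will be used to impute missing data of primary outcome".

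Follow-Up Procedures lists four visits. NIHSS is in the baseline list, which ends "electrocardiogram (ECG), and NIHSS", and at the second visit: "At 10 ± 2 days, we will perform assessments using the PRO-Stroke, repeated routine laboratory tests, ECG, and NIHSS". The two later visits carry other scales: "The mRS, BI, and SS-QOL scores will be determined at 30 ± 3 days and 90 ± 7 days".

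The analysis set is conditional: "All patients in the safety set will be included in the full analysis set if efficacy outcome data are available". The article does not say which efficacy data qualify. The same section states the intention-to-treat principle and announces a sensitivity analysis for missing data without naming a method. It gives no separate rule for patients who die before day 10.

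Sample Size Calculations expects "a mean decrease in the NIHSS score of 3 and 2.1 in the PNS and control groups, respectively, and a standard deviation of 2.5", with a 20% dropout allowance.

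**The concern.** LOCF needs an intermediate measurement to carry. Here there is none, so the method becomes baseline carried forward and the imputed change is 0 for any patient it reaches.

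Zero is a poor value in both directions. For a typical survivor it is too pessimistic, because the plan expects improvement of 2 to 3 points. For a patient who died or deteriorated it is too favourable: if imputed, that patient ranks above a survivor who was measured and had worsened by one point.

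Two consequences follow for the primary comparison. Equal missingness shrinks the treatment difference. Unequal missingness shifts it towards the arm with fewer missing values, even if the drug does nothing. Single imputation also treats the filled-in zeros as if they had been measured.

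The analysis set condition adds a second problem. The reader cannot tell whether LOCF applies to many patients, a few or none.

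**Working it through.** **Step 1. What LOCF can carry.**

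| Visit | NIHSS scheduled? |
|---|---|
| Baseline | Yes |
| 10 ± 2 days | Yes (the endpoint itself) |
| 30 ± 3 days | No (mRS, BI, SS-QOL) |
| 90 ± 7 days | No (mRS, BI, SS-QOL) |

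If the day-10 score is missing, the last observed NIHSS is baseline. Imputed change = baseline − baseline = 0.

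**Step 2. Who is imputed.** The full analysis set condition has three possible readings:
- Day-10 NIHSS is required. LOCF then has nothing to impute, and patients without it are excluded.
- Any efficacy measure after baseline is enough. Patients who die or are lost before day 10 are excluded. LOCF reaches only those with no day-10 NIHSS but some other efficacy measure.
- Baseline NIHSS is enough. Every dosed patient with safety data and no day-10 NIHSS is scored 0.

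The first two exclude patients because an outcome is unavailable, which conflicts with the stated intention-to-treat principle. The last two use the zero score.

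**Step 3. The plan's own sample size.** With difference 0.9, SD 2.5, two-sided α 0.05 and power 90%: n per arm = 2 × (1.960 + 1.282)² × 2.5² / 0.9² = 162.2, so 163 per arm and 326 in total. Allowing for 20% dropout, 326 / 0.8 = 407.5, so 408. The stated 480 is not reproduced, but the LOCF point does not depend on this. The figures below use the planned 240 per arm. For comparison, 192 completers per arm (480 × 0.8 / 2) would give 94.1% power at the full 0.9 difference.

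**Step 4. Effect of scoring 0.** Let q be the share imputed in an arm, μ the true mean improvement and 2.5 the SD among those measured. Missingness is taken as unrelated to outcome. Then:
- mean = (1 − q) × μ
- variance = (1 − q) × 2.5² + q × (1 − q) × μ²
- SE of the difference = √[(variance of PNS + variance of control) / 240]
- rejection rate = 1 − Φ(1.96 − d/SE) + Φ(−1.96 − d/SE), where d is the expected difference.

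The shares q are assumptions. The article gives only an overall 20% dropout.

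Worked case, 20% in both arms: means 0.8 × 3.0 = 2.40 and 0.8 × 2.1 = 1.68, so d = 0.72. The variances are 6.44 and 5.71, SE = 0.225, d/SE = 3.20 and power is 89.3%.

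*Planned effect (3.0 versus 2.1):*

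| Missing, PNS / control | Difference | Power |
|---|---|---|
| 5% / 5% | 0.855 | 96.3% |
| 10% / 10% | 0.81 | 94.5% |
| 20% / 20% | 0.72 | 89.3% |
| 7% / 3% | 0.753 | 91% |
| 25% / 15% | 0.465 | 54% |
| 15% / 25% | 0.975 | 99% |

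*No drug effect (nominal error 5%):*

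| Missing, PNS / control | Both improve 2.1: difference, error | Both improve 3.0: difference, error |
|---|---|---|
| 4% / 6% | 0.042, 5.4% | 0.060, 5.8% |
| 3% / 7% | 0.084, 6.6% | 0.12, 8.2% |
| 5% / 10% | 0.105, 7.5% | 0.15, 10% |
| 15% / 25% | 0.21, 16% | 0.30, 25% |

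The spurious difference equals the gap in missing shares times μ, for example (0.25 − 0.15) × 2.1 = 0.21. It depends on the gap between arms, not on the overall level.

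**The case against.** A reader might infer that every dropout and early death is scored as unchanged. The article does not support this. The full analysis set condition may exclude such patients, and those who attend day 10 and are lost later have a measured score.

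A reader might also infer that missing values concentrate in deteriorating patients, because study medicine stops after a serious adverse event. Stopping the drug is not the same as missing the visit: Data Collection and Management commits investigators to reasonable efforts at follow-up throughout. The concentration is possible, but it is not stated.

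The larger effects above rest on demanding assumptions. The 20% is a dropout allowance in a trial followed to day 90, not a day-10 missing rate. Patients are inpatients, the Discussion expects the short interval to reduce loss, and eligibility excludes those with the highest NIHSS scores or limited survival. With a common 20% rate, a gap as wide as 15% versus 25% would arise by chance with p of about 0.006. At an average of 5% missing, the distortion is small. With equal missingness, type I error stays at 5%, and even 20% missing leaves power near its 90% target.

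Finally, a sensitivity analysis is announced, and an NIHSS at early withdrawal might exist in a full protocol that is not shown.

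These arguments narrow the reach and the likely size. They do not make zero a sensible imputed value, and a sensitivity analysis does not correct the primary estimate. The schedule in the article shows no other NIHSS to carry forward.

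**Conclusion.** The point holds in this form: under the published schedule, LOCF on the primary outcome can only mean no change, which contradicts the improvement that the plan itself expects. The analysis set wording leaves undecided whether patients without a day-10 NIHSS are scored 0 or excluded. That deaths are in fact counted as neutral outcomes is not established, since it follows under only some readings of that wording.

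The size ranges from negligible (error 5.4% at 4% versus 6% missing) to serious (error 16% and, under the planned effect with more missing on PNS, power 54% when the shares are 15% and 25%). These figures assume 240 per arm, SD 2.5, missingness unrelated to outcome and illustrative shares by arm. They describe the readings under which patients are imputed as 0, and do not size the bias from exclusion. The plan should fix this, because the rule governs the primary analysis and changing it before unblinding is cheap. The documents do not show that large harm is likely.

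**What to change.** Before unblinding:

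1. Include all randomised and dosed patients in the primary analysis, whether or not a day-10 NIHSS exists, and reword the full analysis set accordingly.
2. Replace LOCF with multiple imputation by arm under missing-at-random, using baseline NIHSS, age, onset-to-randomisation time, centre, and the 30- and 90-day mRS and BI where available. The later scales will help little for patients lost entirely before day 10.
3. Do not score deaths before day 10 as zero change. Pre-specify their handling, for example worst rank in a rank-based sensitivity analysis. This targets a different quantity from the mean difference, so it should be reported separately.
4. Make the announced sensitivity analysis a delta-adjusted (tipping-point) analysis, and keep LOCF only as a further sensitivity analysis.

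The cost is revised wording, some programming and slightly more complex analysis and reporting. No new data are needed.
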